### Missing Data

If less than 2,5% of an outcome or variable is missing, missing data is handled by case-wise deletion. If more than 2,5% is missing, multiple imputation will be performed using chained equations with predictive mean matching and logistic regression for numerical and categorical variables respectively.^23^ For the imputations all above mentioned variables and outcomes will be used to inform the imputations. 10 datasets will be imputed.

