# Analysis

### Outcome Definitions

The primary outcome is time in days to liberation from mechanical ventilation. Liberation from mechanical ventilation is defined to occur on the second of two consecutive ICU-days without the need for either IV or NIV. Liberation from mechanical ventilation was also considered to occur on the day of ICU discharge if cessation of mechanical ventilation occurs on the same day as ICU-discharge in patients that are not readmitted to the ICU within two days. The competing risk of death is said to occur if patients died before or within 24 hours from liberation from mechanical ventilation. Patients are censored if they were moved to a different hospital while still receiving mechanical ventilation or at 30 days if still receiving mechanical ventilation.

Secondary outcomes are the risk of death from any cause at 30 days, PaO2/FiO2-ratio (PAF-ratio) on the first day of ICU-admission and last measured PAF-ratio in patients dying within 5 days from inclusion.

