### Variables

The explanatory variables of interest are sTM, Syndecan-1 and PECAM-1. These are continuous and presented in ng/ml. They will also be introduced to the regression models as categorical variables divided into three groups: =< 25^th^ percentile, > 25^th^ and =< 75^th^ percentile, > 75^th^ percentile

To be controlled for in the multivariable analyses are the following known predictors of poor outcomes in the ICU: Gender, Age, A history of Chronic Inflammatory Pulmonary Disease (COPD), Septic Shock at ICU-admission, A history of Heart Failure, Worst PAF-ratio on the first day of ICU-admission, The presence of Respiratory Infection at ICU-admission, Acute Kidney Injury during the first day of ICU-admission and highest Bilirubin during first day of ICU-admission.

Septic shock is defined in accordance with the “Third international consensus definition for sepsis” as suspected or confirmed infection plus the need of vasoactive medication to maintain a mean arterial blood pressure of 65 and a blood lactate of 2 or more.^18^

COPD, Heart Failure and Acute Respiratory Infection are adjudicated by one author ([name]) based on information from the EMR without knowledge of the results of the primary outcome or of the values of sTM, Syndecan-1 or PECAM-1.

PAF-ratio is calculated with information from the EMR as the values of PaO2 and FiO2 giving the lowest ratio on a given day of ICU-admission.

Acute Kidney Injury is defined as stage 2 or more from the KDIGO guidelines and calculated based on the worst creatinine during the first day of ICU-admission.^19^ Baseline creatinine is defined as the median of all creatinine levels from 180 to 8 days prior to ICU-admission. In patients without a baseline creatinine, the creatinine levels is estimated with revised Lund-Malmö formula assuming a normal GFR of 70 ml/min/1,73m2.^20^

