### Analysis Methods

The effect of sTM, Syndecan-1 and PECAM-1 on the primary outcome is analysed using cox regression and reported as cause-specific hazards using the method of Ozenne et al.^21^ A separate model is fitted for each of the explanatory variables of interest and each model is controlled for the abovementioned variables.

The effect of the markers of endothelial damage on the risk of death from any cause at 30 days is modelled with cox regression and controlled for the same variables as the analysis of the primary outcome.

We model the effects of continuous variables with restricted cubic splines with 2 knots^22^ if the introduction of splines significantly improves model fit as evaluated by the Wald Statistic.

The effect of the markers of endothelial damage on the PAF-ratio on the first day of ICU-admission and on last PAF-ratio in patients dying within 5 days of inclusion is modelled with linear regression and controlled for COPD, age, respiratory infection and shock (defined as need for vasopressor and a lactate >= 2).

All models will be examined for standard measures of model fit and assumptions and the included variables will be transformed as appropriately. We test for biological plausible interactions such as between levels of the biomarkers of endothelial damage and septic shock or respiratory infection. Interaction terms will be kept in the model if they are significant in the multivariable analysis based on the p-value for the effect of the interaction term.

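### The 2.5% missing-data limit works variable by variable, so it does not cap the patients dropped from a model, and the imputation includes an outcome defined only for early deaths

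*SAP*

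**What the plan says.** The Missing Data section of the SAP sets two rules around one threshold. Below it: "If less than 2,5% of an outcome or variable is missing, missing data is handled by case-wise deletion". Above it: "If more than 2,5% is missing, multiple imputation will be performed using chained equations". The unit in the first rule is the single outcome or variable. No limit is set on the share of patients who are incomplete on at least one item.

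On the content of the imputation model, the section says: "For the imputations all above mentioned variables and outcomes will be used to inform the imputations". No outcome is excepted. Outcome Definitions lists among the secondary outcomes the "last measured PAF-ratio in patients dying within 5 days from inclusion".

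The size of the models follows from two other sections. Variables introduces the adjustment set with "To be controlled for in the multivariable analyses are the following known predictors of poor outcomes in the ICU: Gender, Age" and goes on to name nine covariates in all. Analysis Methods adds: "A separate model is fitted for each of the explanatory variables of interest and each model is controlled for the abovementioned variables". Each Cox model therefore has ten predictors. The PAF-ratio models are smaller, being "modelled with linear regression and controlled for COPD, age, respiratory infection and shock".

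**The concern.** There are two separate problems.

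**The unit of the threshold.** A low limit for case-wise deletion is presumably meant to allow a complete-case analysis only when few patients are lost. Loss in a multivariable model depends on how many patients have any gap, not on how many gaps a single variable has. Every item can pass the 2.5% test while the model as a whole loses several times that share. At stake are precision and, depending on why values are missing, the representativeness of the patients analysed. The SAP gives no sample size, so the cost in precision cannot be judged from the plan.

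**An outcome that does not exist for most patients.** The last PAF-ratio before early death has no value for anyone alive 5 days after inclusion, including patients who die later. Those blanks are not missing data. A chained-equations routine run on the whole cohort cannot tell the difference unless the plan says so.

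**Working it through.** The SAP states no expected loss or missingness rate, so there is no figure of its own to reproduce. What can be checked is the most that the rule allows.

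**Inputs**
- Limit per item: just under 2.5% (Missing Data).
- Covariates in each Cox model: gender, age, COPD, septic shock, heart failure, worst first-day PAF-ratio, respiratory infection, acute kidney injury, bilirubin = 9 (Variables).
- Markers per model: 1 (Analysis Methods). Predictors: 9 + 1 = 10. Counting the outcome: 11.
- Linear PAF-ratio models: 4 covariates + 1 marker + 1 outcome = 6 items (Analysis Methods).

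**Formulas**, for k items each with missing share m
- Independent gaps: 1 − (1 − m)^k
- Gaps that never overlap: k × m
- All gaps in the same patients: m

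**Ceilings at m = 2.5%**
- Cox, 10 predictors: 1 − 0.975^10 = 22.4%; 10 × 2.5% = 25.0%.
- Cox, 11 items with the outcome: 24.3%; 27.5%.
- Cox with age and gender assumed complete, 8 predictors: 18.3%; 20.0%.
- Linear models, 6 items: 14.1%; 15.0%.
- Any model with all gaps in the same patients: below 2.5%.

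Because each item must be below the limit, these values are approached but not reached.

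**Less extreme inputs**
- Ten predictors at 2.0% each: 18.3% (independent); 20.0% (no overlap).
- Ten predictors at 1.0% each: 9.6%; 10.0%.
- Only three or four items at risk, 2.4% each (assumption), independent: 1 − 0.976^3 = 7.0%; 1 − 0.976^4 = 9.3%.

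**Precision**, if events are lost in proportion to patients: a 20% loss widens confidence intervals by √(1/0.80) = 1.118, about 12%. Losses of 7.0% and 9.3% give √(1/0.930) = 1.037 and √(1/0.907) = 1.050, about 4 to 5%.

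**The early-death PAF-ratio.** No arithmetic is needed beyond the threshold. In a whole-cohort dataset this column is blank for everyone who did not die within 5 days. Unless more than 97.5% of the cohort (100 − 2.5) died that early, the blank share exceeds 2.5% and the SAP's own rule sends it to imputation. Predictive mean matching would then take donor values only from the early deaths, assign a last PAF-ratio before death to patients who have none, and use it to predict the other incomplete variables. If the column is left unfilled instead, it cannot serve as a predictor for those patients, and the instruction to use all outcomes cannot be carried out.

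**The case against.** The strongest reply concerns size. Approaching a fifth needs nearly every predictor to sit close to 2.5% missing with little overlap, and the Variables section makes that unlikely. Age and gender are demographics; COPD, heart failure and respiratory infection are adjudicated from the medical record; acute kidney injury has a fallback when no baseline creatinine exists. The items plausibly at risk may be only the marker, PAF-ratio, bilirubin and perhaps one more. This stands. A reader might infer that about a fifth of patients will be lost; the SAP does not support that, because it reports no missingness rates.

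Second, the SAP does not say whether variables under the limit are also imputed once another variable triggers imputation. If they are, deletion disappears in that case. This stands as an ambiguity, but it does not help when every item is under the limit.

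Third, a reader might infer that the primary hazard ratios will be biased because blood gases and bilirubin are taken less often in milder patients or those on NIV. No section says so. Such a pattern would also concentrate the gaps in the same patients and reduce the loss. Complete-case Cox estimates can remain valid if missingness depends only on covariates in the model.

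Fourth, a reader might infer that unprocessed follow-up times enter the imputation. The SAP says only that outcomes will be used and leaves their form open. Using outcomes to inform imputation is sound in principle.

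Finally, an analyst would probably treat the early-death PAF-ratio as not applicable, and no bias from including it has been quantified. That is fair, but leaving it out would depart from the written rule.

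**Conclusion.** Both points hold on the text, at modest size.

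The per-variable limit leaves deletion in a Cox model uncapped: about 22% (independent) to just under 25% (no overlap) at the extreme, about 7 to 9% if three or four items are at risk, and below 2.5% with full overlap. The middle range rests on an assumption about which items are incomplete. The finding is that the rule does not secure a small loss; it does not show that a large one will occur, nor that the estimates will be biased.

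The imputation rule, read as written, includes an outcome that is undefined outside early deaths. That needs no assumption about missingness rates, though its effect on the results is unknown.

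The study is declared exploratory, which limits the weight of both points. A reader might also take the plan to be wrong because "10 datasets will be imputed". That number is not an error; a larger one is a matter of preference. Nor does the SAP fix a transformation of the markers from which a particular scale for imputing them would follow.

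**What to change.** Amend the Missing Data section as follows.

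- Apply the 2.5% limit to the share of patients incomplete on any item of a given model. When it is exceeded, impute all incomplete variables in that model. Say which rule covers exactly 2.5%, which neither does now.
- Leave the last PAF-ratio of patients dying within 5 days out of the whole-cohort imputation, and use it only within its own subset.
- State that the time-to-event outcomes enter the imputation as event indicators plus Nelson-Aalen cumulative hazards for liberation and for death.

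The cost is a few sentences and slightly more analysis work, since some models that would have been complete-case will now be imputed. No new data are needed. Raising the number of imputations is optional.

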### Statistical programming software

All analyses are performed with R version 3.6.1 (The R Foundation for Statistical Computing).

